## Abstract

**Background:**

The management of acute agitation manifesting in patients with schizophrenia or bipolar disorder requires swift pharmacological intervention to provide rapid symptomatic relief and prevent escalation to aggression and violence. Antipsychotic medications are widely used in this setting and the availability of an inhaled formulation with deep lung absorption of the antipsychotic loxapine has the potential to deliver a faster onset of therapeutic effect than the available intramuscular formulations of antipsychotics.

**Methods:**

The efficacy of inhaled loxapine and the alternative antipsychotic aripiprazole delivered via intramuscular (IM) injection will be compared in the Phase IIIb PLACID study. Adults (18–65 years) with a confirmed diagnosis of schizophrenia or bipolar I disorder presenting with acute agitation will be randomly assigned to open-label treatment in a 1:1 ratio. Clinical evaluation will be conducted by raters blinded to treatment assignment. The primary efficacy endpoint is time to response (defined as a Clinical Global Impression of Improvement [CGI-I] score of 1 [very much improved] or 2 [much improved]).

Secondary endpoints will include the percentage of responders at different time points after dosing; the proportion of patients who receive 1 or 2 doses of study drug; time to second dose; time to rescue medication; satisfaction with study drug (evaluated using Item 14 of the Treatment Satisfaction Questionnaire for Medication); and safety and tolerability. Approximately 360 patients will be recruited with an interim analysis conducted once 180 patients have completed the study to decide whether to stop for futility or continue with or without an increase in the sample size up to additional 288 patients.

**Discussion:**

The PLACID trial will assess the efficacy and safety of inhaled loxapine with deep lung absorption compared with the IM antipsychotic, aripiprazole, in acutely agitated patients with schizophrenia or bipolar disorder. In the event that the median time to response of inhaled loxapine is significantly shorter than that of the intramuscular aripiprazole, the PLACID study has the potential to support the inhaled antipsychotic therapy as the standard of care in this setting.

**Trial registration:**

The study protocol was registered with the European Clinical Trials Database on the 31 October 2014 (EudraCT number 2014–000456-29).

**Electronic supplementary material:**

The online version of this article (doi:10.1186/s12888-017-1291-5) contains supplementary material, which is available to authorized users.

## Background

Schizophrenia and bipolar disorder are estimated to affect 21 million and 60 million individuals worldwide, respectively [1]. Agitation, defined as a state of cognitive and motor hyperactivity characterized by excessive or inappropriate motor or verbal activity with an emotional arousal element, is common among patients with schizophrenia or bipolar disorder [2–4]. For these patients, the manifestation of acute agitation represents a serious, disruptive and morbid complication that can escalate rapidly and unpredictably from distress to loss of control and physical aggression and violence towards themselves, other patients and their carers [4–6].

Acute agitation is frequently encountered in both medical and psychiatric emergency settings and should be managed initially with verbal de-escalation and environmental management [7, 8]. Continued escalation of agitation may ultimately require physical restraint and pharmacological treatment [7, 8]. However, such coercive management measures may damage the therapeutic relationship between patients and their carer’s and evoke feelings of panic, fear, powerlessness, anger, frustration, and injustice [2]. The consequence of this negative association of feelings may destroy trust and lead to patient reluctance to seek psychiatric care [3]. Early intervention for acute agitation with a medication delivered via a non-traumatic route has the potential to avoid the negative feelings evoked by a traumatic therapeutic encounter and reinforce the partnership between patient and their carer [2, 3].

The costs associated with agitation, especially agitation that escalates to aggression and violence, among patients with psychiatric disorders may also be considerable although precise estimates of the overall burden are lacking. When inadequately managed, agitation among psychiatric patients can result in an increase in the number and duration of inpatient hospital stays, a reduced likelihood of discharge to community and use of coercive measures and/or escalation to patient violence, presenting a substantial economic burden to the healthcare system [8, 9]. In Spain, the annual cost of psychiatric mechanical restraint has been estimated at €27 million [9]. A separate study conducted in the UK, estimated that the annual cost per psychiatric ward for containment was €267,069 in 2014 [10].

Agitation among patients with psychiatric disorders requires early recognition and swift intervention with treatments that can achieve rapid symptom relief and avoid the progression of agitation to aggression and violence [7]. The acute treatment of agitation associated with schizophrenia or bipolar disorder includes pharmacological tranquilization with oral antipsychotic agents given alone or in combination with benzodiazepines [11–13]. However, while a preferred route of delivery in terms of maintaining a non-traumatic experience for the patient, orally dosed agents may not be optimal in terms of delivering a sufficiently rapid onset of therapeutic effect. Intramuscular (IM) formulations have been shown to provide relatively faster symptomatic relief compared with oral formulation of antipsychotics but have the disadvantage of a potentially traumatic experience for the patient [2, 14].

Inhaled loxapine with deep lung absorption is the first anti-agitation medication available to provide rapid control of agitation combined with a noncoercive non-invasive route of administration. It is administered by inhalation using the Staccato delivery system. The efficacy of inhaled loxapine for the management of agitation among patients with schizophrenia or bipolar I disorder has been confirmed in placebo-controlled, Phase III trials [15–17] and is supported by indirect comparisons with other antipsychotics [18]. However, head-to-head comparisons with other antipsychotics, including those delivered via IM injection, are lacking. Head-to-head trials, often neglected by regulatory authorities and industry sponsors, are important for clinical practice [19]. The PLACID study will compare inhaled loxapine and IM aripiprazole (considered a standard of care in this setting; [20]) for the prompt stabilization of acutely agitated patients with schizophrenia or bipolar disorder.

## Methods

The PLACID study will evaluate the efficacy, defined as time to response (Clinical Global Impression of Improvement [CGI-I] or 1 or 2) of inhaled loxapine as compared with aripiprazole administered via IM injection in acutely agitated patients with schizophrenia or bipolar disorder.

Inhaled loxapine is available in 10 mg dose, being the delivered dose 9,1 mg, a maximum of 2 doses can be administered during 24 h (24). For IM aripiprazole the standard dose is 9,75 mg with a possibility of two additional doses during 24 h (14). In this study a maximum of 2 doses of both study drugs are allowed [14, 21].

The study will be conducted at up to 30 centres across Europe including centres in the Czech Republic, Germany, Russia and Spain and will include male and female patients aged between 18 and 65 years with a confirmed diagnosis of schizophrenia or bipolar I disorder according to Diagnostic and Statistical Manual of Mental Disorders (DSM-5) criteria.

### Design

The PLACID study is a Phase IIIb, open-label, rater blind, randomised, active control, prospective, parallel group, multicentre clinical trial (Fig. 1, Table 1). The study will be conducted in two phases. The first phase will enrol approximately 180 patients who will be randomly assigned (in a 1:1 ratio) to open-label treatment. Clinical evaluation will be carried out by personnel blinded to treatment assignment. Patients will be instructed not to tell the blinded assessor which treatment they received.

**Fig. 1 Fig1:**
[figure not shown]
Study design

**Table 1 Tab1:** PLACID study flow

Procedure	Pre-treatment period		Post-treatment evaluation period									
	Screening^a^ *(up to 4 h)*	Baseline *(within 30 min prior to dose 1)*	Time 0					1 h		2 h	4 h	24 h or end of the agitation episode, whichever occurs first
			0 min	10 min	20 min	30 min	50 min	60 min	90 min	120 min	240 min	
Informed consent^b^	X											
Inclusion/exclusion criteria	X	X^c^										
Demographics	X											
Medical history	X											
Pre-dose medications	X^d^	X^d^										
Physical examination^e^	X											X
Urine pregnancy test (females of child-bearing potential)^f^	X											
Randomisation		X										
Study drug administration			X	← NOT ALLOWED →							Up to 1 dose PRN^g^	
CGI-S Scale^h^		X										
CGI-I Scale^h^				X ± 2 min	X ± 2 min	X ± 2 min	X ± 2 min	X ± 5 min	X ± 5 min	X ± 5 min		X ± 1 h
TSQM (Item 14)^h^										X		X
Vital signs^h,i^		X						X		X	X	X
AEs^j^			X→	→	→	→	→	→	→	→	→	X
Concomitant medications^k^	X→	→	→	→	→	→	→	→	→	→	→^k^	X^k^
Discharge from the study												X

*AE* adverse event, *CGI-I* Clinical Global Impression of Improvement, *CGI-S* Clinical Global Impression of Severity, *eCRF* electronic case report form, *HCG* human chorionic gonadotropin, *ICF* informed consent form, *PRN* pro re nata (as needed), *TSQM* Treatment Satisfaction Questionnaire for Medication. ^a^Patients must remain in the study centre during screening. ^b^The approved ICF must be signed by patients with consent capacity before completing any protocol-specific procedures. ^c^Inclusion criteria #3 and 4 and Exclusion criteria 4 and 12 will be assessed at baseline. ^d^All medications taken within 30 days of the study start, includind medications taken in the 24 hours prior to the first dose of study medication, should be recorded on the eCRF. ^e^Baseline and end-of-study examinations will be completed; other examination should be a focused physical examination at the discretion of the Investigator based on the patient's circumstances. ^f^Females of documented postmenopausal status and inpatients who previously tested negative for pregnancy (serum β-HCG) upon admission are not required to undergo the urine test at screening. ^g^Note that patients who only receive one dose of study drug (Dose 1) may not be given rescue medication (unless medically required). Rescue medication may be administered per the Investigator's judgement from 20 minutes after Dose 2 of the study medication has been given (and after the 2-hour efficacy assessments have been completed). ^h^At all time points, perform rating scales/ assessments in the following order, as applicable: CGI, TSQM (Item 14), vital signs. ^i^Pulse, systolic and diastolic blood pressure and respiraion rate will be recorded. ^j^AEs will be recorded for at least 24 hours after Dose 1 or the study medication or the end of the agitation episode as per the Investigator's judgement, whichever occurs first. Patients should be monitored for bronchospasm for => 1 hour after Dose 1 and Dose 2 (if Dose 2 is administered). ^k^Concomintant medications, including those to treat AEs, will include all medications that patients were already taking at the time of screening or started during the course of the study. If rescue medication is taken, the time that it is taken will be recorded. Whether rescue medication has been taken by 4 hours and by 24 hours after Dose 1 or the end of the agitation episode as per the Investigator's judgement, whichever occurs first, will be recorded

An interim analysis will be performed on the phase 1 data to determine whether to continue into phase 2 or to stop the trial due to futility or unfeasibility. The final sample size of the PLACID study will be re-calculated based on the interim analysis results. The two-phase design with interim analysis is justified due to the limited availability of CGI-I data during the first 2 h’ post-administration both for inhaled loxapine and IM aripiprazole, and therefore making difficult the sample size estimation. Data demonstrating meaningful improvements from baseline on the CGI-I scale at 120 mins post dose are available [15, 16, 20, 22] for both treatments, but data demonstrating the time course of these improvements during the first two hours of treatment, when rapid and effective action is required to minimise the risks associated with acute agitation, are lacking.

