### Study treatments

Baseline evaluations will be performed as close as possible to, and within 30 min before, administration of initial study medication. Patients will be randomly assigned to receive either inhaled loxapine 10 mg (delivered dose 9.1 mg) using the hand-held, portable, *Staccato* delivery system or IM aripiprazole 9.75 mg per 1.3 mL dose. Patients will receive a maximum of 2 doses of either study drug with the second dose given if required at least 2 h after the first dose.

Randomisation will be achieved using an interactive voice response system and will be stratified according to the patient’s disease type (schizophrenia or bipolar I disorder).

The planned duration of participation in the study will be up to approximately 30 h consisting of a screening and baseline phase of up to 4.5 h and a post-treatment period which will commence with the administration of the first dose of study drug and will continue for at least 4 h and up to a maximum of 24 h.

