### Outcomes and endpoints

The primary efficacy endpoint is time to response measured during the first 2 h after the first dose. Response is defined as a CGI-I score of 1 (very much improved) or 2 (much improved). Secondary endpoints will include: the proportion of patients achieving response at 10, 20, 30, 50, 60, 90 and 120 min after the first dose of study drug; the total number of patients who receive 1 or 2 doses of study drug without rescue medication by 4 h and 24 h after the first dose of study drug; time to rescue medication; time to the second dose of study drug; and satisfaction with study drug (evaluated using Item 14 of the Treatment Satisfaction Questionnaire for Medication [TSQM]; [24]). Safety and tolerability will also be assessed through the reporting of adverse events, physical examination, recording of vital signs.

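### Recording of AEs, rescue and second dose stops at an outcome-dependent time between 4 h and 24 h, although the dose/rescue endpoint is set at a fixed 24 h; crude 24-h comparisons can be biased toward the arm discharged earlier

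*Protocol article*

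**What the plan says.** All references are to the protocol article.

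- **Table 1, last column.** The final visit is headed "24 h or end of the agitation episode, whichever occurs first". It holds the last AE and concomitant-medication entries and discharge from the study.
- **Table 1, footnote j.** "AEs will be recorded for at least 24 hours after Dose 1 or the study medication or the end of the agitation episode", with the Investigator judging the end of the episode and the earlier time applying.
- **Table 1, footnote k.** "Whether rescue medication has been taken by 4 hours and by 24 hours after Dose 1 or the end of the agitation episode" is to be recorded, under the same judgement and the same earlier-of rule.
- **Study treatments.** The post-treatment period "will continue for at least 4 h and up to a maximum of 24 h". A second dose falls inside it: "second dose given if required at least 2 h after the first dose".
- **Outcomes and endpoints.** One secondary endpoint counts patients given one or two doses "without rescue medication by 4 h and 24 h after the first dose of study drug". No end-of-episode limit is attached. Time to rescue and time to second dose are also listed. The primary endpoint is "time to response measured during the first 2 h after the first dose".
- **Statistical analysis.** Secondary analyses are exploratory and safety is descriptive.

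**The concern.** A patient whose episode is judged over at 5 h may leave the study then. Nothing is recorded for hours 5 to 24, yet one endpoint is expressed at 24 h. How long a patient is watched depends on how the patient fares, and treatment is open-label. The article describes blinding for the clinical raters and does not say whether the Investigator who judges the end of the episode is blinded.

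If the arms differ in time to end of episode, the arm that leaves earlier has less time in which an AE, a second dose or rescue can be seen. Crude proportions to the last visit then differ even when the true risks are equal. Censoring time to rescue and time to second dose at the end of the episode would be informative for the same reason. At stake are the head-to-head safety description and the 24-h secondary endpoint, in a trial whose abstract says it may support a standard of care.

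**Working it through.** **1. The passages side by side**

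| Item | Stop of recording | Horizon of the result |
|---|---|---|
| AEs | Footnote j: a minimum of 24 h, and also the earlier of 24 h and end of episode | Descriptive, no horizon given |
| Rescue | Footnote k: 4 h and 24 h, or end of episode if earlier | Fixed 4 h and 24 h |
| Second dose | Not named in j or k; ends through discharge at the last visit | Fixed 4 h and 24 h |
| Whole period | Study treatments: minimum 4 h, maximum 24 h | – |

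Footnote j contradicts itself, because a minimum of 24 h cannot hold together with an earlier stop. It also conflicts with the 24-h maximum. Footnotes j and k state no 4-h minimum. Read alone, footnote k would let an early end of episode cut even the 4-h rescue record. Read with Study treatments, and with the 240-min column that precedes the last visit in Table 1, 4 h is kept.

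**2. Size under assumptions**

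The plan gives no figure on this point, and no event rates or episode durations, so every input below is assumed except the 4-h and 24-h limits.

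- True 24-h risk R = 20% in both arms.
- Follow-up T = min(24, 4 + E), with E exponential of mean m hours. Mean follow-up = 4 + m(1 − e^(−20/m)).
  - m = 4: 8.0 h
  - m = 6: 9.8 h
  - m = 12: 13.7 h
- *Constant hazard:* λ = −ln(0.80)/24 = 0.0093 per hour. With k = λ + 1/m, the observed proportion is 1 − e^(−4λ)·[(1/m)/k·(1 − e^(−20k)) + e^(−20k)].
- *Early-clustered events:* a share f falls before 4 h and the rest is uniform over 4–24 h. The observed proportion is R·[f + (1 − f)(mean follow-up − 4)/20].

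| Mean follow-up, arm A v arm B | Constant hazard | f = 0.5 | f = 0.8 |
|---|---|---|---|
| 8.0 v 8.0 h | ratio 1.00 | 1.00 | 1.00 |
| 8.0 v 9.8 h | 7.1% v 8.6%, 0.82 | 12.0% v 12.9%, 0.93 | 16.8% v 17.2%, 0.98 |
| 8.0 v 13.7 h | 7.1% v 11.8%, 0.60 | 12.0% v 14.9%, 0.81 | 16.8% v 17.9%, 0.94 |
| 13.7 v 8.0 h | 11.8% v 7.1%, 1.67 | 1.24 | 1.07 |

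With follow-up fixed at 24 h in both arms the ratio is 1.00. True risks of 10% and 40% give similar ratios (0.59 and 0.62 in place of 0.60). These are not bounds: 6.0 v 13.7 h (m = 2 and 12) under constant hazard gives 0.46.

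**3. What is not touched**

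The primary endpoint closes at 2 h, inside the 4-h minimum. The 4-h endpoint is complete in every patient if that minimum is kept.

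**The case against.** **Direction.** A reader might infer that loxapine, expected to act faster, will be watched for less time and so will look safer. The documents do not support that. Faster response is the hypothesis under test, and it concerns the first 2 h. Faster onset need not bring an earlier end of episode after 4 h, no durations are given, and the sign reverses if the aripiprazole arm ends earlier. This objection stands.

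**Handling of early leavers.** A reader might also infer that patients discharged early are counted as free of rescue at 24 h. The article does not say how they enter the 24-h endpoint, and that may properly be left to an analysis plan that is not shown. This stands too, but no analysis plan can recover events that were never recorded.

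**Size.** Large distortions need a constant hazard and a wide gap in follow-up. For instance, an assumed 30% risk with 6 h v 10 h observed gives λ = −ln(0.70)/24 = 0.01486 and 1 − e^(−6λ) = 8.5% v 1 − e^(−10λ) = 13.8%, an apparent 38% reduction. After one or two acute doses, with peak plasma levels at 2–3 min and 1 h (Discussion), early clustering is plausible and the distortion shrinks.

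**Meaning of the endpoint.** Rescue and second dose treat the current episode, so once it is over, no further treatment may be a genuine outcome. Bias then arises only if renewed agitation before 24 h is meant to count, which the article leaves open. This does not apply to AEs.

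**Stakes.** The affected analyses are exploratory or descriptive, and bronchospasm is separately monitored for at least 1 h after each dose. That limits the weight of the point without removing it.

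**Conclusion.** The point holds in a conditional form. As written, AE and rescue recording, and through discharge the second dose, end at an Investigator-judged, outcome-dependent time between 4 h and 24 h. The dose/rescue endpoint is set at a fixed 24 h, and footnote j contradicts itself. Crude 24-h comparisons are distorted only if the arms differ in time to end of episode, and then toward the arm discharged earlier, in either direction.

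In the scenarios taken as the main range, the ratio under equal true risks is about 0.6 to 0.98 when the first arm leaves earlier, and 1.07 to 1.67 when an 8.0 v 13.7 h gap is reversed. These figures rest wholly on assumed risks, durations and event timing. They show what could happen and do not forecast this trial. The primary analysis is not affected. The point should be settled before the safety tables and 24-h secondary results are produced.

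**What to change.** 1. Reconcile footnotes j and k, the last column of Table 1, Study treatments, and Outcomes and endpoints, so that they give one stopping rule for data recording. State explicitly that recording never stops before 4 h.
2. Make the common 0–4 h window the main between-arm comparison for AEs, rescue and second dose. The 4-h dose/rescue endpoint is already planned.
3. Label longer-window results as running to 24 h or end of episode, and report observation time by arm beside them. Do not read them as 24-h risks unless these items are recorded to 24 h in every patient, for example from the chart of those still in hospital.

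Two familiar alternatives do not solve the problem. Cumulative incidence with discharge as a competing event equals the crude proportion when every patient is followed to event, discharge or 24 h. Rates per person-hour mislead when events cluster early: with f = 0.8 and 8.0 v 13.7 h, the rate ratio is about 0.94 × 13.7/8.0 = 1.6 against the arm discharged earlier, with no true difference.

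Cost: rewording and a few extra tables, plus a chart check if 24-h risks are wanted. The drawback is that later events carry less weight in the main safety comparison. For the second dose, allowed from 2 h, the window leaves 4 − 2 = 2 h of observation.

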### Patients

The study population will consist of patients meeting DSM-5 criteria for schizophrenia or bipolar I disorder experiencing an acute episode of agitation, both hospitalized and attending to a psychiatric or general emergency room.

To be eligible to participate patients must be clinically agitated at baseline with a value ≥4 for the Clinical Global Impression of Severity (CGI-S; [23]) scale and otherwise in good health. Patients will be specifically excluded from participation if their agitation is judged to be caused primarily by acute alcohol or drug intoxication/withdrawal. Those patients judged to be at serious risk for suicide will also be excluded. Patients treated with benzodiazepines or other hypnotics or oral or short-acting IM antipsychotics within 1 h prior to study drug administration will be excluded although those patients may be subsequently reassessed for inclusion. Other exclusion criteria will include pregnancy or breastfeeding, a history of or current significant hepatic, renal, gastroenterologic, respiratory, cardiovascular, endocrinologic, neurologic or haematologic disease as well as acute or active airways disease.

All patients will be required to provide written informed consent prior to undergoing any study procedure. Patients considered by appropriately qualified staff to be of impaired capacity to provide informed consent will not be eligible for participation. In Spain a proxy or deferred informed consent is possible. If patients have recovered the capacity, they will be asked to provide the informed consent; otherwise the data will not be used in the analysis.

